## Methods

### Participants and Eligibility

Inclusion criteria are as follows: (1) veterans enrolled in the San Francisco VA Health Care System (SFVAHCS), (2) those recommended or scheduled for major elective surgery within the next 6 months (eg, general, spinal, thoracic, vascular, urological, gynecological, orthopedic, or other surgeries), (3) those currently (ie, past 30 d) smoking a minimum average of 1 cigarette per day, (4) those having daily access to a personal smartphone device and Wi-Fi, and (5) those open to receiving smoking-cessation interventions. Veterans followed by primary care who are referred to external institutions for major elective surgery will also be eligible.

Exclusion criteria will be evaluated through medical record review and clinical assessment: (1) psychotic, bipolar, or neurocognitive disorders or other psychiatric or medical conditions judged to be unstable in the past 30 days; (2) untreated, current, active problem gambling, as assessed by a medical record diagnosis or a Problem Gambling Severity Index (PGSI) score ≥8; (3) enrollment in end-of-life or palliative care; (4) surgery with a clinical indication for cancer; (5) unable to meet time commitment; (6) currently pregnant or planning to become pregnant during the study [21]; (7) a suicide attempt, or suicidal ideation with intent, within 30 days prior to enrollment; and (8) concurrent participation in another tobacco cessation trial.

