#### Outcome Measures

##### Smoking Measures

Smoking cessation outcomes will be administered at baseline and posttreatment. A Nicotine and Tobacco Use Survey (NTUS) developed internally will assess age at first use, duration of use, use of all forms of nicotine and tobacco, prior quit attempts (ie, intentionally not smoking for ≥24 h), duration of cessation (if any), and presence of other tobacco users in the home. Posttreatment assessment will include frequency and duration of quit attempts in the past 30 days. The Fagerström Test for Nicotine Dependence (FTND) [39] is a validated instrument of the severity of physiological addiction to nicotine. The Contemplation Ladder [40] is a validated single-item measure of motivation to quit smoking. The Questionnaire of Smoking Urges [41,42] is a validated 10-item measure that assesses cigarette craving and withdrawal. It will also be administered weekly to assess craving via 1 item, *“*I have a desire for a cigarette right now,” via a scale from 0 (strongly disagree) to 100 (strongly agree) [42]. The Timeline Followback (TLFB) [43,44] is a validated, staff-administered instrument that uses anchor dates to prompt recall of substance use. It will be used to document cigarette, tobacco, electronic nicotine delivery system (ie, e-cigarette), cannabis, any other substance uses, and TUD medications. Participants who are in CM condition will be assessed at screening for past 30-day use, at weekly sessions for past 7-day or days since the last TLFB assessment, and at follow-up visit for days since the last TLFB assessment; participants who are in TAU condition will be assessed at screening for past 30-day use and at follow-up visit for days between the last TLFB assessment and follow-up assessment. Bioverification using mobile CO monitor will also be used to verify abstinence at follow-up visit. If there is inconsistency between self-report and bioverified CO level, a salivary cotinine test might be adopted as needed.

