#### TAU Condition

Control participants will receive usual care at the SFVAHCS: (1) referral to the Tobacco Cessation Clinic and (2) referral to the VA’s free Telephone Quitline, “TeleQuit” (known as “Quit VET”). The Tobacco Cessation Clinic is a consult service that proactively calls patients 3 times to offer pharmacological and behavioral smoking cessation treatment. Veterans will also be provided with information on accessing Quit VET, a national toll-free number available to veterans that allows them to speak with a smoking cessation counselor for up to 5 sessions [50]. At week 6, participants receiving TAU will document their participation in these interventions via self-report, and a medical chart review will be conducted to collect information regarding their engagement.

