#### Exploratory Outcomes

Seven-day point prevalence of cigarette abstinence will be assessed post treatment, defined as (1) no smoking for 7 days prior (via TLFB) and (2) CO levels ≤6 ppm. For individuals with CO levels >6 ppm, who report smoking cannabis via TLFB and are not receiving NRT, salivary cotinine <10 ng/ml will be used [47,51]. Cutoffs are recommended by the SRNT (Society for Research on Nicotine and Tobacco) guidelines [47].

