### Data Analytic Plan and Monitoring

The results will be reported using CONSORT (Consolidated Standards of Reporting Trial) guidelines [52], and analyses will be conducted using IBM SPSS and R software (R Core Team, R Foundation). Analyses will employ an intent-to-treat approach, which includes all randomized participants regardless of treatment adherence. As-treated analyses will also be conducted to examine change in smoking cessation outcomes as a function of treatment adherence. The procedure for as-treated analyses will include intervention adherence variables (ie, feedback/counseling session attendance and medication adherence) and their interactions with treatment conditions as predictors in the models. Continuous outcome variables will be checked for normality, homoskedasticity, linearity, and missingness. Descriptive analyses, repeated measures ANOVA (rmANOVA), and generalized linear mixed models (GLMMs) will be conducted to confirm study feasibility (aim 2). Descriptive analyses will include bivariate associations between demographic variables, time, and outcome variables (recruitment, engagement, and retention) via chi-squared tests, *t* tests, and correlations. rmANOVA will use time (2 levels: baseline and end-of-treatment) as the predictor. GLMMs will be used to analyze CM attendance and video uploads, in addition to intervention efficacy (aim 3*),* and posttreatment 7-day point prevalence of cigarette abstinence. Differences between treatment groups on quit attempts, mean cigarettes per day, and severity of nicotine dependence across time will be analyzed through GLMMs, with predictors of time, intervention condition, and the time-by-treatment interaction, implemented via the *lme4* and *WeMix* packages in R [53,54].

Sensitivity analyses will be used to test the influence of missing data and the assumptions related to missing data. If there is substantial missingness or attrition (>10%), we will address the missing items using multiple imputation via the *mice* package in R and conduct sensitivity analyses incorporating “inverse-probability of censoring” weights to account for attrition.

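### Post-treatment abstinence is assigned to a mixed model although each participant contributes one binary record, so a participant random intercept cannot be identified (minor)

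*Protocol article*

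**What the plan says.** **Abstinence.** Under Data Analytic Plan and Monitoring, GLMMs are assigned to CM attendance, video uploads, intervention efficacy "and posttreatment 7-day point prevalence of cigarette abstinence". Exploratory Outcomes fixes the timing: "Seven-day point prevalence of cigarette abstinence will be assessed post treatment". The outcome combines 7 days without smoking on the Timeline Followback (TLFB) with a CO reading of 6 ppm or less. Smoking Measures adds: "Bioverification using mobile CO monitor will also be used to verify abstinence at follow-up visit". Table 1 shows exhaled CO at week 6 only.

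The next sentence of the analytic plan describes GLMMs "with predictors of time, intervention condition, and the time-by-treatment interaction", but for quit attempts, cigarettes per day and dependence severity. Abstinence is not in that list. No random-effect structure is given for it and no cluster level is named. Recruitment is from one health care system, and participants must be "those currently (ie, past 30 d) smoking a minimum average of 1 cigarette per day".

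**As-treated analysis.** The same section says these analyses will "include intervention adherence variables (ie, feedback/counseling session attendance and medication adherence) and their interactions with treatment conditions as predictors in the models". CM participants have five weekly sessions of about 15 to 20 minutes. TAU participants get a Tobacco Cessation Clinic referral and "referral to the VA’s free Telephone Quitline", with up to 5 counselor sessions. Other Data Documentations says TAU session numbers are tracked; TAU Condition says this is done at week 6 by self-report and chart review.

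**The concern.** A mixed model separates variation between participants from variation within them, which takes repeated records per participant or some other grouping. Here each participant supplies one yes/no value. A logistic GLMM with a participant intercept then contains a variance that the data say nothing about, and its arm effect is an odds ratio conditional on that variance. The reported odds ratio could therefore reflect the fitting routine rather than the trial.

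This matters because abstinence is the only between-arm outcome defined with bioverification; quit attempts, cigarettes per day and nicotine dependence are self-reported. A conditional odds ratio from an unidentified model could be carried into the planning of a larger trial.

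The as-treated model raises a second, smaller question: what an arm-by-attendance coefficient would mean when sessions differ in kind between arms and attendance is itself an outcome of follow-up.

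**Working it through.** **Inputs.** From the article: 18 per arm (Power Analysis); one abstinence record per person (Exploratory Outcomes, Table 1). Assumed, because no abstinence rates are given: 7/18 in CM and 3/18 in TAU. The plan states no figure for this analysis; the minimum n of 16 in Power Analysis concerns the repeated measures ANOVA and has no bearing here.

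**1. One record per person.** With a random intercept of SD s, the probability of abstinence in an arm with linear predictor η is p(η, s) = E[1/(1 + exp(−(η + sZ)))], Z standard normal. The log-likelihood is the sum over arms of e·ln p + (n − e)·ln(1 − p). For any s, η can be chosen so that p equals the observed proportion, so the maximum is the same for every s:

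−2 log L = −2[7 ln(7/18) + 11 ln(11/18) + 3 ln(3/18) + 15 ln(15/18)] = 40.277.

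Solving for η in each arm (Gauss-Hermite quadrature, 80 nodes):

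| Random-intercept SD | −2 log L | η CM | η TAU | Log OR | Odds ratio |
|---|---|---|---|---|---|
| 0 | 40.277 | −0.452 | −1.609 | 1.157 | 3.18 |
| 1 | 40.277 | −0.546 | −1.906 | 1.360 | 3.90 |
| 2 | 40.277 | −0.744 | −2.566 | 1.822 | 6.18 |
| 4 | 40.277 | −1.235 | −4.237 | 3.002 | 20.1 |
| 6 | 40.277 | −1.766 | −6.059 | 4.292 | 73.1 |

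The fitted proportions are 0.389 and 0.167 in every row. Other assumed counts behave the same way: with 8/18 versus 3/18 the log-likelihood is −20.475 at SD 0, 0.5, 1, 2 and 4, while the log odds ratio runs 1.386, 1.454, 1.636, 2.198 and 3.626.

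**2. Would a baseline record help?** No. Eligibility makes baseline abstinence about 0/18 in each arm. In a model with time, arm and their interaction, the baseline log-odds then run to minus infinity (separation). The baseline rows contribute a likelihood of 1, which leaves the single-record problem above. Table 1 also shows no baseline CO reading.

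**3. Would weekly records help?** Not for this outcome. Weekly TLFB and CO uploads belong to the CM protocol (Table 2). TAU has TLFB at screening and follow-up, and CO at follow-up only, so there is no bioverified weekly series in TAU.

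**4. What the same counts do support.** Risk difference = 7/18 − 3/18 = 0.222. Wilson 95% limits are 0.203 to 0.614 for 7/18 and 0.058 to 0.392 for 3/18. Newcombe limits:

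- lower: 0.222 − √[(0.389 − 0.203)² + (0.392 − 0.167)²] = −0.070
- upper: 0.222 + √[(0.614 − 0.389)² + (0.167 − 0.058)²] = 0.472

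That is 22 percentage points, 95% CI −7 to 47, whatever is believed about a random intercept.

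**5. As-treated interaction.** Take the design matrix [1, arm, sessions, arm × sessions] with 18 + 18 participants and illustrative session counts. With TAU counts recorded, the rank is 4 of 4, even if only 2 of 18 TAU participants attend anything. It falls to 3 of 4 if every TAU participant is coded zero, which is not what the article describes. The term can therefore be estimated; the difficulty is its meaning:

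| | CM | TAU |
|---|---|---|
| Sessions | Five scheduled weekly sessions, counseling with feedback on CO readings | Optional clinic contacts or up to 5 quitline sessions |
| How recorded | In the course of study-delivered sessions | Self-report and chart review at week 6 |
| TUD medication on TLFB | Weekly | Screening and follow-up only |

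**The case against.** The article specifies no random effect for abstinence. The sentence with model terms covers other outcomes, and random-effects detail is commonly left to an analysis plan not shown here. If the authors use the term GLMM loosely for a logistic model without a random effect, nothing goes wrong. That is fair, and it is why the point is about wording. But the article does name a mixed model for an outcome measured once, and a version without a random effect is not a mixed model.

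A reader might infer that the arm comparison itself becomes arbitrary. It does not: the fitted proportions and the maximized likelihood are the same at every SD, so a likelihood-ratio test of arm is unaffected. Only the conditional odds ratio is undetermined, and the value of 73 needs an SD of 6. No fit in lme4 or WeMix was run, so what the software would print is not shown.

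A reader might also infer that session attendance exists only in CM, so that the as-treated interaction cannot be estimated. The article contradicts this, since TAU sessions are tracked; only the CM feedback element is peculiar to CM. Nor can medication adherence be treated as measured alike in both arms, given the TLFB schedules. Finally, intent-to-treat comes first in the plan and the as-treated analysis is an addition, not offered as the randomized effect. That relapse would drive attendance is a reasonable worry, but nothing in the article demonstrates it.

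**Conclusion.** The concern holds for abstinence. With one binary record per participant, no named cluster and near-zero baseline abstinence by eligibility, a participant random intercept is not identifiable. The conditional odds ratio can be 3.2 or 20 on identical data and identical fit (SD 0 versus 4, assumed counts 7/18 and 3/18). The non-identifiability does not depend on those counts; the particular odds ratios do. It does depend on reading GLMM as a model with a participant-level random effect, the only grouping the described data offer.

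For the as-treated model, the supportable point is narrower: the attendance interaction is estimable but hard to interpret, because it combines unlike sessions recorded differently and conditions on behavior after randomization.

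Severity is minor. Abstinence is exploratory, efficacy is expressly unpowered, and the feasibility outcomes do not depend on this model.

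**What to change.** 1. Remove abstinence from the GLMM list. State instead that 7-day point prevalence abstinence will be compared by the risk difference with a Newcombe or score 95% CI. Add a logistic model with arm and the two randomization strata (sex; 10 or more versus fewer than 10 cigarettes per day), with no random effect, and with Firth's penalty if events are sparse. Other exact or score methods would serve equally well.
2. Report session attendance within each arm as descriptive, stating what counts as a session in TAU and how it was recorded.
3. Label every adherence interaction, including that for medication adherence, as non-randomized, and note that TLFB medication data are collected on different schedules in the two arms.

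The cost is analysis wording only; no data collection changes. The article reports 18 of 36 participants randomized and no blinding of the study team, so the change is best made before outcome data are analyzed.

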### Randomization and Blinding

Eligible participants will be randomly assigned to either CM or TAU in a 1:1 ratio, stratified by (1) biological sex and (2) cigarettes per day (≥10 or <10 cigarettes per day) using random permuted blocks via REDCap. We will examine subgroups in exploratory analyses. Due to staffing constraints, no member of the study team will be blinded.

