### Power Analysis

Because the nature of aim 2 was primarily to examine feasibility, we aimed only to observe large effects (*f*=.40) with a modest degree of power (β=.80). The results of the power analysis based on rmANOVA with α=.05 indicate that the proposed sample size (n=18 per condition) is adequate for proposed analysis (minimum n=16). Because intervention efficacy is an exploratory aim in this pilot test, we are not attempting to power the analyses for aim 3.

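### For cigarettes per day and FTND, the stated time-by-arm model uses the baseline value inefficiently and, for cigarettes per day, ignores stratification on baseline smoking; adjusting for continuous baseline is more precise at almost no cost

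*Protocol article*

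**What the plan says.** Data Analytic Plan and Monitoring compares the arms by GLMM on three outcomes: quit attempts, daily cigarette consumption and dependence severity. The model is specified as one "with predictors of time, intervention condition, and the time-by-treatment interaction". No other covariate is named for these comparisons; adherence variables are added only in the as-treated models.

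Under Randomization and Blinding, allocation to the two arms is equal and is described as "stratified by (1) biological sex and (2) cigarettes per day (≥10 or <10 cigarettes per day) using random permuted blocks via REDCap". The only analysis statement beside the stratification factors is that subgroups will be explored.

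Under Smoking Measures, "Smoking cessation outcomes will be administered at baseline and posttreatment". The analysis section gives two time levels for the repeated-measures ANOVA: "rmANOVA will use time (2 levels: baseline and end-of-treatment) as the predictor". Seven-day abstinence is a post-treatment outcome only (Exploratory Outcomes). Power Analysis says that "the proposed sample size (n=18 per condition) is adequate for proposed analysis (minimum n=16"), and that the efficacy comparison is exploratory and not powered.

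**The concern.** The baseline value of each continuous outcome is collected, and randomization makes the arms equal at baseline in expectation. A model with free arm means at both times does not use that fact. It estimates a baseline arm difference and subtracts it in full, where regression on baseline would subtract only the predictable part. The price is a wider interval for the arm effect.

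There is a second, related loss for cigarettes per day. Stratifying on 10 or more versus fewer than 10 cigarettes per day forces the arms to be similar at baseline on that outcome. A change-score contrast without that information reports a standard error as if allocation had been unrestricted.

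What is at stake is the precision of the two continuous efficacy estimates that this pilot passes on. With 36 participants and no power target for efficacy, the analysis model is one of the few places where precision can still be gained.

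**Working it through.** **Inputs from the document.** 18 per arm; 1:1 allocation stratified by sex and cigarettes per day; outcomes at baseline and post-treatment; fixed effects time, arm and time-by-arm; f = 0.40, α = .05.

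**Assumptions.** Pre-post correlation ρ is not given, so a range of .3 to .9 is shown. The between-arm effect is taken as 0.8 SD, the two-group equivalent of f = 0.40. SDs are equal before and after, and outcomes are treated as normal.

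**The plan's own figure.** For a two-group, two-occasion repeated-measures ANOVA, λ = N·m·f²/(1 − ρ). With N = 16, m = 2 and an assumed ρ = .5, λ = 16 × 2 × 0.16 / 0.5 = 10.24 on 1 and 14 df, giving power .845. The smallest N reaching .80 is 15, or 16 with equal arms. The stated minimum of 16 is therefore reproduced as a total at ρ = .5.

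**Precision of the two analyses.** In units of the outcome variance, the change score has variance 2(1 − ρ) and the baseline-adjusted outcome 1 − ρ². Their ratio is (1 + ρ)/2. The SE of the arm difference is √(2/18 × variance). Power is from the noncentral t, with 34 df for change and 33 df for adjustment.

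| ρ | Variance, change | Variance, adjusted | Ratio | SE, change | SE, adjusted | Power, change | Power, adjusted |
|---|---|---|---|---|---|---|---|
| .3 | 1.40 | 0.91 | .65 | .394 | .318 | .50 | .69 |
| .5 | 1.00 | 0.75 | .75 | .333 | .289 | .65 | .77 |
| .7 | 0.60 | 0.51 | .85 | .258 | .238 | .85 | .90 |
| .9 | 0.20 | 0.19 | .95 | .149 | .145 | >.99 | >.99 |

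With unequal SDs s0 (baseline) and s1 (post), the variance difference is (s0² + s1² − 2ρ·s0·s1) − s1²(1 − ρ²) = (s0 − ρ·s1)². It is never negative, but it vanishes if s0 = ρ·s1, so similar SDs are part of the claim.

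**Adding the stratified allocation.** The table ignores stratification. Trials of 36 were therefore simulated with allocation stratified on a dichotomised baseline, as for cigarettes per day, and analysed by change score without the stratum.

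| ρ | Mean model SE | True sampling SD | Type I error |
|---|---|---|---|
| .3 | .39 | about .35 | about .03 |
| .5 | .33 | .31 | .034 |
| .7 | .257 | .246 | .038 |

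The planned contrast is thus mildly conservative. Putting the stratum into the change-score model (a stratum-by-time term) brought type I error back to about .05 and raised power at ρ = .3 from .50 to .61. Adjusting for continuous baseline instead gave power, planned versus adjusted, of .51 versus .69 (ρ = .3), .66 versus .76 (.5) and .87 versus .90 (.7), with no gain at .9. A rerun moved these powers by less than .02.

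**What the strata add by themselves.** Adding both strata as main effects to the planned mixed model left the time-by-arm estimate unchanged (largest difference 2 × 10⁻¹⁵; mean SE .325 without, .323 with). Adding them to the baseline-adjusted model when they carried nothing beyond baseline moved the mean SE from .288 to .297.

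**The case against.** **The analysis is valid and exploratory.** This stands. The time-by-arm contrast is unbiased, its type I error is at or below nominal, and Power Analysis says efficacy is not powered. No decision rule depends on the gain. The smoking outcomes also sit under a heading that calls them primary, but that is a separate labelling matter.

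**An unseen analysis plan may add covariates.** Possible. The article does, however, fix a predictor list for these outcomes, so the point is about a stated choice and not a missing detail.

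**The reduction to change scores is not certain.** The two time levels are stated for the repeated-measures ANOVA. Timeline Followback covers every day to the end of week 6 and is taken weekly in the CM arm, so cigarettes per day could enter at more occasions. The figures hold for two time points and a linear model, and are approximate for count or skewed data.

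**Stronger readings that the document does not support.** A reader might infer that baseline is left out. It is the first level of the response, and is used inefficiently. A reader might infer that omitting both strata costs precision in every model. As main effects they do not change the interaction, and the cigarettes-per-day stratum adds nothing useful once continuous baseline is present. Inverting (1 + ρ)/2 suggests the gain equals a trial of 55, 48 or 42 participants instead of 36; that ignores both the stratified allocation and the lost degrees of freedom. Likewise √(2/18) = one third of an SD is the baseline imbalance under unstratified allocation. With allocation stratified at the median of a normal baseline it is about 0.2 SD.

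**Conclusion.** The point holds for cigarettes per day and FTND, as a precision improvement of low to moderate importance. In power terms the gain is about .18 at a correlation of .3 (.69 − .51), .10 at .5 (.76 − .66) and .03 at .7 (.90 − .87), and nothing near .9. These figures rest on an assumed 0.8 SD effect, an assumed correlation, similar pre and post SDs, two time points, complete data and a linear model. For cigarettes per day, part of the gain comes from correcting a standard error that is too wide because the model ignores stratification on baseline smoking. The material does not show that the planned analysis is invalid, or that forcing both strata into the quit-attempt or abstinence models would help with 18 per arm.

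**What to change.** For cigarettes per day and FTND, analyse the post-treatment value with arm and the continuous baseline value of that outcome as predictors. Equivalently, keep the mixed model but constrain the arms to a common baseline mean. For cigarettes per day, the continuous baseline can stand in for its stratum. Add sex where numbers allow, and state beforehand that it is dropped if one sex is too sparse. In the quit-attempt and abstinence models, adjust for baseline cigarettes per day (or its stratum) only if event numbers permit.

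The cost is one or two sentences of analysis text and 1 to 3 degrees of freedom; every covariate is already collected. Data collection runs to April 2027 and no interim analysis is planned, so the change can still be made. Since no study team member is blinded, it should be dated and recorded before outcomes are compared by arm.

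### The sensitivity analyses are meant to test the missing-data assumptions, but the named methods, multiple imputation and censoring weights, ordinarily share one assumption and cannot test it

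*Protocol article*

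**What the plan says.** All of the missing-data plan stands in the protocol article under Data Analytic Plan and Monitoring.

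- **Purpose:** "Sensitivity analyses will be used to test the influence of missing data and the assumptions related to missing data".
- **Handling, when triggered:** "If there is substantial missingness or attrition (>10%), we will address the missing items using multiple imputation via the *mice* package in R".
- **Sensitivity method named:** the plan will also "conduct sensitivity analyses incorporating “inverse-probability of censoring” weights to account for attrition".
- **Efficacy model:** differences in quit attempts, cigarettes per day and dependence "will be analyzed through GLMMs, with predictors of time, intervention condition, and the time-by-treatment interaction".
- **Analysis set:** "Analyses will employ an intent-to-treat approach, which includes all randomized participants regardless of treatment adherence".

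The seven-day abstinence definition (Exploratory Outcomes) combines TLFB with a CO cutoff. It does not say how a participant with no follow-up assessment is counted.

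On data collection (Smoking Measures), CM participants give TLFB at each weekly session, but "participants who are in TAU condition will be assessed at screening for past 30-day use and at follow-up visit". A footnote to Table 1 adds that cigarette smoking may be reassessed at week 0.

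**The concern.** The plan states a purpose and names tools that do not serve it. In a cessation trial the missing-data assumption most open to doubt is that those who stop responding smoke like comparable participants who keep responding. Someone who has relapsed may well be the person who misses the follow-up visit. Multiple imputation, censoring weights and the likelihood-based mixed models all ordinarily rely on missing at random, so all three can be wrong together.

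The assumption also has different support in the two arms. In CM, a relapse recorded at a weekly session or on a CO video can inform the imputation or the weights. In TAU no smoking measurement falls between screening (or week 0) and follow-up. The only post-baseline information is on treatment engagement, such as session counts and chart review.

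At stake is how the arm comparison is described. Readers could take agreement between the two analyses as evidence that the missing-data assumption was tested, when it was not.

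**Working it through.** **1. When the plan applies.** The trigger is more than 10% missingness or attrition. For attrition, 0.10 × 36 = 3.6, so 4 or more participants. With 18 per arm, one participant is 1/18 = 5.6 percentage points of an arm.

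**2. What each method assumes.**

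| Method | Working model | Assumption as ordinarily used |
|---|---|---|
| GLMM | outcome over time | missing at random |
| Multiple imputation (mice) | outcome given observed data | missing at random |
| Censoring weights | dropout given observed data | missing at random |

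No section names an analysis that departs from the last column: no delta shift, tipping point, worst case or rule counting missing as smoking.

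**3. Does agreement give a warning?** A large-sample simulation (n = 400,000) let dropout depend on the unseen outcome. All rates are assumptions: true abstinence 0.26 in TAU and 0.50 in CM, true difference 0.24, and 5% of abstainers dropping out. The imputation and weight models used arm and a baseline covariate only. The entries below are the estimated CM minus TAU difference.

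| Smokers dropping out (TAU / CM) | Imputation | Weights | Missing = smoking | Shared bias of the first two |
|---|---|---|---|---|
| 20% / 20% | 0.247 | 0.247 | 0.228 | 0.247 - 0.24 = +0.007 |
| 35% / 15% | 0.190 | 0.190 | 0.227 | 0.190 - 0.24 = -0.050 |
| 15% / 35% | 0.307 | 0.307 | 0.228 | 0.307 - 0.24 = +0.067 |

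Imputation and weighting agree to three decimals in every row. Both overstate abstinence within each arm: 0.293, 0.336 and 0.281 against 0.26 in TAU, and 0.540, 0.526 and 0.588 against 0.50 in CM. The bias in the difference takes either sign.

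**4. The same at 18 per arm.** Assume completer abstinence of 50% in CM and 25% in TAU. If dropouts resemble completers in their arm, the difference is 0.25 for any dropout pattern. If all dropouts smoke, it is 0.50 × (18 - d_CM)/18 - 0.25 × (18 - d_TAU)/18:

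- 2 CM, 2 TAU: 0.444 - 0.222 = 0.22
- 4 CM, 4 TAU: 0.389 - 0.194 = 0.19
- 6 CM, 2 TAU: 0.333 - 0.222 = 0.11
- 2 CM, 6 TAU: 0.444 - 0.167 = 0.28

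**5. What a delta analysis would show.** Assume 5 CM and 2 TAU dropouts (7/36 = 19%) and observed abstinence of 7/13 and 3/16. This ignores the weekly CM data. Multiply the dropouts' odds of smoking by k, so that their abstinence probability is 1/(1 + k × 6/7) in CM and 1/(1 + k × 13/3) in TAU.

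| k | CM | TAU | Difference |
|---|---|---|---|
| 1 | (7 + 5 × 0.538)/18 = 0.538 | (3 + 2 × 0.188)/18 = 0.188 | 0.351 |
| 2 | (7 + 5 × 0.368)/18 = 0.491 | (3 + 2 × 0.103)/18 = 0.178 | 0.313 |
| 5 | (7 + 5 × 0.189)/18 = 0.441 | (3 + 2 × 0.044)/18 = 0.172 | 0.270 |
| all smoke | 7/18 = 0.389 | 3/18 = 0.167 | 0.222 |

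The difference falls from 35 to 22 points without changing sign. Even with every CM dropout smoking and every TAU dropout abstinent it is 7/18 - 5/18 = 0.11. Neither planned method would report this range.

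**The case against.** **The opening sentence is general.** It does not say that the listed methods are the only ones, and an article condenses a fuller plan. This stands in part: a further method may exist, and mice can run delta adjustment. But the article chose to state the purpose and name the tools, and none of those named departs from missing at random. It would be too much to infer that the team will claim robustness without testing it; the document does not say so.

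**The two methods differ.** Imputation is how missing items are handled, and the weights are the sensitivity analysis. Their working models differ, so comparing them does check model specification. This stands, but it is a different check from the one promised.

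**The size is chosen.** A reader might infer from the 35-versus-22-point example that the plan overstates the CM benefit by 13 points. The documents do not support that. They give no dropout or abstinence rates, the example leaves out CM's weekly TLFB, craving and CO data, and the bias can favour either arm. Under equal dropout among smokers, imputation is closer to the truth (+0.007) than counting missing as smoking (0.228 - 0.24 = -0.012). Missing = smoking is therefore itself an assumption and not an automatic safeguard.

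**TAU is not imputed from baseline alone.** Session counts and the week 6 chart review supply post-baseline engagement data (Other Data Documentations; TAU Condition). This stands, but these are not measurements of smoking.

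**The stakes are low.** The Power Analysis section calls efficacy exploratory and does not power it, and seven-day abstinence is an exploratory outcome. In the example above, Fisher's exact test on 7/13 versus 3/16 gives p = 0.064 and the Wald interval runs from about 2 to 68 points, so evidence is weak before any departure. This limits the weight of the point and argues against a rule based on whether an interval crosses zero. It does not close the gap between purpose and method, and quit attempts, cigarettes per day and dependence still appear under a primary-outcomes heading.

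**Conclusion.** The concern holds in a limited form. The stated aim of testing the missing-data assumptions is not met by the methods named, because imputation and censoring weights ordinarily share the missing-at-random assumption and their agreement cannot reveal unseen relapse among dropouts. The unequal smoking data by arm make the assumption harder to support in TAU.

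The effect on the arm difference is of unknown size and sign. With the assumed rates above, the shared bias ran from -0.050 to +0.067 on a true difference of 0.24; these figures illustrate the mechanism and do not predict this trial's result. The simulation used no post-baseline predictors, so informative weekly CM data could reduce the bias in that arm. The change should be made, with modest consequence, since efficacy is exploratory and unpowered in a 36-person pilot.

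**What to change.** 1. Keep multiple imputation, and state that its models use the available post-baseline data: weekly TLFB, craving and CO results in CM, and treatment engagement in TAU.
2. Keep the censoring weights, labelled as a second analysis under missing at random.
3. Add delta-adjusted imputation in mice, with shifts set separately by arm. A few values suffice, for example the dropouts' odds of smoking multiplied by 1, 2 and 5, plus all dropouts smoking as one scenario. For cigarettes per day, shift imputed values toward the participant's baseline.
4. Report how the estimated arm difference moves across the scenarios and where it changes sign, or that it does not within the range. Keep this descriptive and do not judge it by whether an interval crosses zero.

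The cost is a few lines of R in a package already named and one extra table, and the result may look less favourable. The article expects data collection to end in April 2027 with no interim analysis, so this can still be specified in advance. If it is not added, the statement that the assumptions will be tested should be withdrawn.
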